### Outcomes

Baseline assessments were conducted by trained research assistants at the study schools. Mid-intervention (6-months) and post-intervention (12-months) assessments will also be conducted at the study schools. For consistency and accuracy, a protocol manual, which includes specific instructions for conducting all assessments, was developed and will be used by research assistants. Questionnaires were completed before the physical assessments in exam-like conditions and physical assessments were conducted in a sensitive manner (e.g., weight measured in a discreet, private setting). Demographic information including age, gender, ethnicity, language spoken at home and mother/father’s highest level of school was collected at baseline. A range of primary and secondary outcomes and hypothesized mechanisms of behavior change will be measured.

### Primary outcomes

#### Physical activity

PA will be assessed using triaxial Actigraph accelerometers (GT3X and GT3X+), which will be worn by participants during waking hours for seven consecutive days, except while bathing and swimming. Trained research assistants, following standardized accelerometer protocols [55], will fit the monitors and explain the monitoring procedures to students. Data will be collected and stored in 10-second intervals. The mean activity counts per minute (CPM) and daily step counts will be calculated, thresholds for activity counts will be used to categorize PA into sedentary, light, moderate and vigorous intensity activity [56].

#### Cardio-respiratory fitness

Cardio-respiratory fitness (CRF) will be assessed using a 20 m multistage fitness test [57]. Participants will be required to run back and forth between two lines over a 20 m distance within a set time limit. Running speed will start at 8.5 km/hour and will increase by 0.5 km/hr each minute using the Multi-stage test cadence CD. Participants will be instructed to run in a straight line and to place one foot over the 20 m line before the next beep. The test is completed when a participant fails to reach the line for two consecutive shuttles. Scores will recorded as the level and shuttle reached, which will be converted to the number of 20 m laps completed to provide a continuous variable for analysis.

#### Fundamental movement skill competency

FMS competency will be assessed using the Test of Gross Motor development (TGMD) II [44]. The TGMD II includes six locomotor (i.e., run, gallop, hop, leap, horizontal jump, slide) and six object control (i.e., striking a stationary ball, stationary dribble, kick, catch, overhand throw, and underhand roll) skills. Participants will perform each skill twice and skills will be video-taped for assessment. Inter-rater and intra-rater reliability will be established (> 80%) using pre-coded video-tapes before movement skills are assessed.

### Secondary outcomes

#### Height and weight

Weight will be measured in light clothing without shoes using a portable digital scale (Model no. UC-321PC, A&D Company Ltd, Tokyo Japan) to the nearest 0.1 kg. Height will be recorded to the nearest 0.1 cm using a portable stadiometer (Model no. PE087, Mentone Educational Centre, Australia). Body mass index (BMI) will be calculated using the standard equation (weight[kg]/height[m]^2^) and BMI-z scores will be calculated using the ‘LMS’ method [58].

#### Self-concept

Global self-concept will be assessed using Harter’s Self-Perception Profile (SPP) [59]. The SPP utilizes a four-choice structured alternative format to reduce socially desirable responses. Participants must first decide which of the two statements best describes them and then choose whether the statement is ‘sort of true’ or ‘really true’ for them. Each item is scored from 1 (*low-self-perception*) to 4 (*high self-perception*).

#### Resilience

Participants will complete the Child and Youth Resilience Measure (CYRM-28) [60]. Based on a validation study involving children from 11 countries, the CYRM-28 was found to have good content-related validity and provide a culturally sensitive measure of youth resilience [61]. The CYRM-28 has 28 items and includes three sub-scales: individual, relationships with primary care-givers, and contextual factors that facilitate a sense of belonging. Items are rated on a 5-point Likert scale with values ranging from 1 (*Not at all*) to 5 (*A lot*).

#### Screen time

Participants will complete six items related to weekday and weekend day recreational screen time from the Health Behavior in School-aged Children (HBSC) study [62]. The HBSC screen time questions compare favorably with other measures in sedentary behavior [63] and has acceptable reliability in children, with intraclass correlation coefficients ranging from 0.86 (95% CIs, 0.76–0.92) for watching television on school days to 0.38 (95% CIs, 0.10–0.60) for using the internet for non-school purposes and chatting on line [64].

### Hypothesized mediators of behavior change

A poor understanding of the mechanisms of behavior change in PA interventions has been noted in the literature [65,66]. Students, parents and teachers will complete a range of scales assessing individual and socio-environmental level mediators of PA behavior change.

#### Perceived sport competence

Perceived sport competence will be assessed using a subscale from Harter’s SPP [59].

#### Enjoyment

Enjoyment of PA will be assessed using the Physical Activity Enjoyment Scale (PACES) [67]. The 16-item scale is scored on a 5-point Likert scales, with responses ranging from 1 (*Disagree a lot*) to 5 (*Agree a lot).*

#### Social support

Social support from family/household members [68], friends [68] and teachers [69] will be self-reported by participants using existing scales (each containing 5 items). All scales utilize 5-point Likert scales with responses ranging from 1 (*never*) to 5 (*always*). Parents will also report the level of social support they provide for their children using the Children’s Leisure Activities Study Survey (CLASS) [70].

#### Environment

Parents will complete selected scales from the CLASS assessing children’s access to PA facilities and equipment in their home and local community [70]. Parents will also report barriers and facilitators to their children’s PA in the local community using the CLASS. Teachers at the study schools will report on their schools’ physical environment and facilities and students’ access to these within and beyond the school day using scales selected from the New South Wales Schools Physical Activity and Nutrition Survey (SPANS) [71].

### Process evaluation

A range of process data will be collected to complement the outcome data. Process measures will include i) teacher and student attendance at workshops (i.e., percentage attendance), ii) student leadership accreditation (i.e., number of students who complete the workshop and satisfy the accreditation guidelines), iii) teacher satisfaction with professional learning workshops (using workshop evaluation questionnaires at the end of Phase 1), iv) parental involvement will be determined using a process evaluation questionnaire (e.g. reading newsletters and completion of home-based FMS tasks) and attendance at the parent evening, v) teacher, student and parent satisfaction with all intervention components (using process evaluation questionnaires at the completion of the study), vi) compliance with PA policies will be determined through interviews with school Principals, vii) PE intervention fidelity will be determined (using SOFIT observations). PE lessons will be observed at baseline, 6- and 12-months using the System for Observing Fitness Instruction Time (SOFIT) tool [72]. Percentage of lesson time spent in MVPA and time dedicated to skill development will be assessed. All teachers of Stage 2 students (both intervention and control groups) will be observed at each time point.

### Statistical methods

The study will be adequately powered to detect clinically important changes in the three primary outcomes at the 12-month assessments. Statistical analyses of the primary and secondary outcomes will be conducted using linear mixed models with PROC MIXED in SAS V 9.1 (SAS Institute Inc, Cary, NC) and alpha levels will be set at *p* < 0.05. The mixed models will be specified to adjust for the clustered nature of the data and will follow the intention to treat principle. Potential moderators of the intervention effects (e.g., ethnicity, socio-economic status and type of school) will be explored using linear mixed models. Differences between participants in the intervention and groups at baseline and differences between completers and those who drop out of the study will be examined using Chi square and independent samples t-tests in PASW Statistics 17 (SPSS Inc. Chicago, IL) software. Hypothesized mediators of PA behavior change will be examined using multilevel linear analysis and a product-of-coefficients test that is appropriate for cluster randomized controlled trials [73].

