### Sample size calculation

Power calculations were conducted to determine the sample size required to detect changes in the three primary outcomes [i.e., PA, cardiorespiratory fitness (CRF) and FMS] at the 12-month assessments. All calculations assumed baseline-posttest correlation scores of 0.80 and were based on 80% power with alpha levels set at *p* < 0.05. Using the standard deviation (SD = 33) and intraclass correlation coefficient (ICC = 0.05) values from the Kinder-Sportstudie (KISS) [42], it was calculated that a study sample of N = 440, with 8 clusters (i.e. schools) of 55 students would provide adequate power to detect an achievable between group difference of 11 moderate-to-vigorous physical activity (MVPA) minutes/day [42]. Based on data from the Action Schools BC! (SD = 13) [43] and the KISS (ICC = 0.03) [42] studies, a sample of 440 would also provide adequate power to detect a between group difference of 4 laps on the multi-stage fitness test (i.e., CFR outcome). In the absence of existing ICC values for FMS outcomes, an ICC estimate of 0.05 and a SD of 15 units [44] indicated that the study would be adequately powered to detect a between group difference of 5 units on the TGMD-II gross motor quotient.

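### The between-arm baseline comparison uses child-level chi-square and t-tests although schools were randomised, so chance differences would be flagged well above the nominal 5%

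*Protocol article*

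**What the plan says.** All of the following is from the protocol article.

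- **Statistical methods, supporting comparisons.** One sentence covers two comparisons: the arms at baseline, and children who finish against children who leave. Both "will be examined using Chi square and independent samples t-tests in PASW Statistics 17". That sentence appears to have lost the word control before groups; I read it as intervention versus control. The unit compared is the participant, and no allowance for school is mentioned.
- **Statistical methods, outcomes.** For the primary and secondary outcomes the same paragraph says: "The mixed models will be specified to adjust for the clustered nature of the data". It also calls for a mediation test suited to cluster-randomised trials.
- **Blinding and randomization.** Schools, not children, were allocated. They were matched in pairs on size and socio-economic position, and baseline assessments came before randomisation.
- **Setting and participants.** 460 children consented in eight schools.
- **Sample size calculation.** The intraclass correlation (ICC) is 0.05 for physical activity, 0.03 for fitness and 0.05 for movement skills, with 55 children per school.

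**The concern.** Arm is constant within a school. Any tendency of children in one school to resemble each other therefore feeds directly into the difference between arms, and a test that counts every child as independent understates the standard error of that difference. The plan recognises this in its sample size, its outcome models and its mediation analysis. The baseline comparison, specified between the outcome and mediation sentences, is the exception.

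There is a second reason not to want these p-values. Baseline data were collected before schools were randomly allocated, so any difference between arms arose by chance. Even a test with the correct standard error would be testing a hypothesis already known to be true.

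What is at stake is the reading of the baseline table. With only eight schools some imbalance is to be expected, and these tests would label a good part of it as significant. That could lead readers to doubt a sound randomisation.

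**Working it through.** **The plan's own figure.** The article gives no error rate for the baseline tests. The nearest stated figure is the sample size, and it reproduces with a standard design effect. For physical activity, the SD of a change score with correlation 0.80 is 33 × √(2 × (1 − 0.80)) = 20.87. For a difference of 11 min/day, 80% power and two-sided 5%, n per arm = 2 × (1.960 + 0.842)² × 20.87² / 11² = 56.5, so 57. The design effect is 1 + (55 − 1) × 0.05 = 3.70. Then 57 × 3.70 = 211 per arm, or 211/55 = 3.83 schools, rounded up to 4 per arm: 8 × 55 = 440, as stated. The sample size is not in dispute here; the plan evidently treats children in a school as correlated.

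**Inputs for the baseline tests.**
- Children per school: 460/8 = 57.5 (Setting and participants); 55 in the sample size calculation.
- ICC: 0.03 and 0.05 (Sample size calculation). Applying them to baseline values is an assumption.
- Nominal level: two-sided 5%. The article sets 0.05 for the outcome analyses, does not state sidedness, and gives no separate level for the baseline tests.

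**Formula.** Design effect DE = 1 + (m − 1) × ICC. An unadjusted test understates the standard error by a factor of √DE, so its actual false-positive rate is 2 × (1 − Φ(1.96/√DE)).

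| m | ICC | DE | √DE | 1.96/√DE | Actual rate |
|---|---|---|---|---|---|
| 57.5 | 0.03 | 2.70 | 1.64 | 1.19 | 23.3% |
| 57.5 | 0.05 | 3.83 | 1.96 | 1.00 | 31.6% |
| 55 | 0.03 | 2.62 | 1.62 | 1.21 | 22.6% |
| 55 | 0.05 | 3.70 | 1.92 | 1.02 | 30.8% |

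**Check by simulation.** Eight schools of 55, randomised within four pairs, 10,000 runs per scenario and no benefit from matching. At ICC 0.03 and 0.05 the t-test rejected 23.2% and 31.2% of the time, and the chi-square test 22.7% and 30.7%. With an assumed spread of 30 to 88 children per school, the t-test rejected 25.0% and 33.6%.

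**Credit for matching.** The article does not say how much between-school variance the pairing removes. Taking one half as an illustration, the simulated rates fall to 14.5% (ICC 0.03) and 19.4% (ICC 0.05). A direct approximation agrees: DE becomes (1 − ICC) + m × ICC/2, which at m = 55 is 0.97 + 0.825 = 1.80 and 0.95 + 1.375 = 2.33, giving about 14% and 20%.

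**Lower ICC.** At ICC 0.01 and m = 57.5, DE = 1.565 and the rate is 11.7%.

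**Completers versus dropouts.** Here the groups being compared occur within the same schools, so the full design effect does not apply. The approximate design effect uses the product of the variable's ICC and that of dropout. With both at 0.05 it is 1 + 56.5 × 0.05 × 0.05 = 1.14, which gives 2 × (1 − Φ(1.96/√1.14)) = 6.7%. Simulation with an assumed 15% dropout and a dropout ICC of 0 to 0.05 (5,000 runs each) gave 5.0% to 6.7%.

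**The case against.** The strongest reply is that nothing important depends on these tests. The outcome models allow for clustering, so does the mediation analysis, and the article nowhere says that a significant baseline difference will choose covariates, trigger a further analysis or serve as a verdict on the randomisation. This stands. A reader might infer that the treatment-effect estimates are compromised, or that covariates will be picked on baseline p-values; the article supports neither.

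The rate also depends on conditions. The article gives ICCs only for the three primary outcomes, and the one for movement skills is an estimate made for want of published values. It gives none for age, gender or the other demographic variables, some of which may hardly vary by school. The pairing of schools should earn some credit. Both points stand: 23% to 32% is not a rate for the whole baseline table. Even so, the illustrative matched figures are three to four times nominal.

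Finally, it may be said that if baseline p-values are uninformative anyway, how often they cross 0.05 hardly matters. In part that is right, and it is why the remedy is to drop the tests instead of correcting them. The rate is still useful, because it shows how often the table would mislead if the tests were reported as planned.

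**Conclusion.** The point holds for the between-arm baseline comparison. The article fixes an analysis that ignores the unit of randomisation, out of line with the rest of the same paragraph; this is a stated choice and not a detail left to another document. At the plan's own ICCs and 57.5 children per school, with no credit for matching, the false-positive rate is about 23% to 32% instead of 5%. It is about 15% to 19% if matching removed half of the between-school variance, and lower for variables with smaller ICCs. The harm is confined to false signals of baseline imbalance.

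Two stronger readings are tempting and not supported. One is that strongly school-patterned variables would be flagged almost half the time. That needs an ICC near 0.10, which the article does not give, and a plausible example such as parental education is likely to be related to the socio-economic position on which schools were paired. The other is that the dropout comparison suffers to the same degree. Completers and dropouts share schools, and the inflation is slight under the assumptions above. It could be larger if dropout were strongly concentrated in particular schools, but nothing in the article indicates that.

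**What to change.** Replace the baseline significance tests with a table by arm giving mean and SD or n and %, with standardised differences and no p-values. As a minor consistency point, compare completers with dropouts using a model that includes a school effect, for example a logistic mixed model with a random effect for school.

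The cost is one sentence in the analysis section and a little programming. Design, sample size, data collection and outcome models are unchanged.

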## Discussion

In this paper we described the rationale and study protocol for the SCORES intervention. To the authors’ knowledge, SCORES is the first PA and FMS intervention targeting Australian primary school children in low-income communities. Targeting children of low SEP is important because they have reduced access to PA opportunities and are typically less active and skilled than youth of middle and high SEP [11,12]. By Year 4, students should achieve mastery in a range of FMS, however, recent data suggests that the prevalence of advanced skills is low among Australian children and proficiency levels have declined since 2004 [11].

Although there is strong evidence that school-based PA interventions are effective in increasing the duration of PA and increasing CRF in children and adolescents, their impact on leisure time PA and FMS is less convincing [14-16]. Such programs are typically evaluated among youth transitioning from childhood to adolescence, a period of time that is characterized by an erosion of activity patterns [19,74]. Nevertheless, recent well-designed studies [42,43,75], such as the KISS intervention [42] have demonstrated that multi-component school-based interventions can increase PA and CRF in children. However, these studies have involved daily PE lessons, which may not be feasible in many schools.

Alternatively, interventions that provide professional learning opportunities for teachers and promote PA within existing PE lessons and throughout the school day (i.e., lunch time and recess) may provide a valuable framework for sustainable practice. Unfortunately, many primary school teachers lack the confidence and skills to teach PE effectively [40,76], which may explain their reluctance to teach this subject in favor of traditional academic subjects (e.g., mathematics and science). The lack of focus on teacher professional learning in school-based PA interventions is surprising considering the importance placed on professional learning in the general education literature [77] and that teachers have specifically stated that professional development in PE, and teaching FMS in particular, is urgently needed and a high priority for improving PA-related outcomes in primary schools [76].

SCORES is an innovative multi-component school-based intervention targeting primary school children in low-income communities. The strengths of this study include the study design, the objective measures of PA, FMS and CRF and the comprehensive multi-component intervention. The findings from the study may be used to guide teacher pre-service education, professional learning and school policy in primary schools.

## Abbreviations

CLASS: Children’s leisure activities study survey; CMT: Competence motivation theory; CYRM-28: Child and Youth Resilience Measure; HBSC: Health behavior in school-aged children; MVPA: Moderate-to-vigorous physical activity; PACES: Physical activity enjoyment scale; PA: Physical activity; Self-determination theory; SPP: Self-perception profile; SPANS: Schools physical activity and nutrition survey; System for observing fitness instruction time; TGMD-II: Test of gross motor development II.
